### Secondary outcome measures

Changes in routinely collected liver enzymes by blood testing.Digital histological quantification of intrahepatic fat.Correlations with BMI and image-determined anthropometric measurements, for example, subcutaneous adipose tissue, visceral adipose tissue volumes and muscle mass.Grade of steatosis scores [the Non-alcoholic Fatty Liver Disease Activity Score proposed by the Non-alcoholic steatohepatitis Clinical Research Network (NAS–CRN)] from routine histology reporting.Postoperative outcomes, including perioperative mortality and morbidity (Clavien-Dindo classification, Comprehensive Complication Index and International Study Group for Liver Surgery complications).Change in health-related quality of life by measurement of EQ-5D Score.

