### Statistical analysis and power calculation

Our previous work reported a mean (±SD) HFF of 4 (±2)%.^105^ Following chemotherapy, we estimate at least a 50% increase in HFF that is, increase to mean (SD)=6%±2.5%. We have planned a recruitment of at least 35 patients. As attrition (for multiple reasons) is common in this type of study, of the 35 patients, we conservatively estimate that 25 patients will have complete data from at least 2 MR evaluations. The resultant power is 98% (alpha: 0.05; within-person correlation: 0.7).

For the LiMAx testing, which is more frequent in the study schedule, we estimate at least 32 patients (10% attrition rate) will have complete data from two LiMAx tests. Based on the Lock *et al* study in patients undergoing preresection chemotherapy^73^ (mean (±SD): 340±95 vs 391±82 µg/kg/hour), the resultant power is 84% (alpha: 0.05; within-person correlation: 0.7).

Statistical support will be provided where required by the University of Manchester Cancer Data Science Team. The main analysis will focus on intrapatient change in both liver function (measured by the LiMAx test) and HFF (measured by advanced MRI), which occurs subsequent to chemotherapy, and their recovery prior to surgery. These changes will be related to subsequent clinical course, CT volumetry and histopathological analysis of the resected liver. We will explore the use of analysis of variance (ANOVA) methods and mixed-effects methods to account for within-person correlations. For each timepoint, standard approaches to categorical (χ^2^ test) and continuous (Mann-Whitney U test) variables will be used. Correlation matrices will be constructed to assess relationships between LiMAx and HFF with other continuous variables using Spearman’s Rank Correlation Coefficient.

To account for multiple testing, a p value of <0.01 will be considered to indicate statistical significance. Predictors of HFF at each timepoint will be explored using multivariable linear regression models. To reduce the anticipated right skewness of the distributions, logarithmic transformation will be explored.

Because of the large number of variables and the anticipated high levels of correlations, we will use factor-cluster methods. There will be at least five clusters: patient-related factors; routine blood measures; CT-derived anthropometrics; LiMAx readouts and MR readouts. Separate models will be developed for each cluster and significant (p<0.05) variables selected for the final model.

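### Per-kg LiMAx is correlated, unadjusted, with BMI: if liver capacity rises less than in proportion to weight, a negative correlation appears without any liver pathology

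*Protocol article*

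**What the plan says.** The only place the article gives the LiMAx unit is the power calculation (Statistical analysis and power calculation), where the cited values are "340±95 vs 391±82" in µg/kg/hour. It does not spell out that the kg is the patient's body weight, but that is the natural reading.

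The same section states: "Correlation matrices will be constructed to assess relationships between LiMAx and HFF with other continuous variables", with Spearman rank coefficients. The section Secondary outcome measures lists "Correlations with BMI and image-determined anthropometric measurements, for example, subcutaneous adipose tissue, visceral adipose tissue volumes and muscle mass". The significance rule is that "a p value of <0.01 will be considered to indicate statistical significance", and for LiMAx "we estimate at least 32 patients (10% attrition rate) will have complete data from two LiMAx tests".

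LiMAx readouts and CT-derived anthropometrics also form two of the variable clusters for the modelling, and HFF is to be modelled at each timepoint. The article mentions no weight adjustment, no absolute LiMAx and no weight-conditional correlation.

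**The concern.** Per-kg LiMAx is absolute capacity divided by weight. BMI is weight divided by height squared. The planned correlation therefore has weight in the denominator of one variable and the numerator of the other. If a heavier patient does not have proportionally more liver capacity, the per-kg value falls as weight rises, and BMI rises with it.

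The article presents the study as informative for obesity-related cancer mechanisms. A finding that liver function is lower at higher BMI would answer a listed secondary outcome and would be easy to report as biology. It could come partly or wholly from the scaling.

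**Working it through.** **Plan's own figure.** The article gives no figure for this correlation, so there is nothing to reproduce.

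**Inputs from the article.** n = 32 for LiMAx, 25 for MR, and a threshold of 0.01. The per-kg LiMAx CV is 95/340 = 0.28 in one group and 82/391 = 0.21 in the other. The corresponding log SDs, from sqrt(ln(1+CV²)), are 0.274 and 0.207.

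**Assumptions, not in the article.**
- Weight CV 18%, so log SD sqrt(ln(1+0.18²)) = 0.179.
- Height CV 5.5%, and weight-height correlation 0.4.
- Capacity proportional to weight^b times noise with log SD about 0.22. No true link of capacity with obesity beyond b.
- b from 0 to 1.

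**Step 1, weight-BMI correlation.** log BMI = log weight - 2 log height.
- Variance: 0.179² + 4×0.055² - 4×0.4×0.179×0.055 = 0.0284, SD 0.1685.
- Covariance with log weight: 0.179² - 2×0.4×0.179×0.055 = 0.0242.
- Correlation: 0.0242/(0.179×0.1685) = 0.80.

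**Step 2, built-in correlation.** On the log scale, r = -0.80 × (1-b)×0.179 / sqrt([(1-b)×0.179]² + 0.22²). Spearman rho = (6/π) × arcsin(r/2). The last two columns are simulated at n = 32, where p<0.01 needs |rho| of about 0.449.

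| b | r | rho by formula | rho simulated | p<0.01 |
|---|---|---|---|---|
| 0 | -0.80×0.179/0.284 = -0.50 | -0.49 | about -0.48 | 61% |
| 0.5 | -0.80×0.0895/0.2375 = -0.30 | -0.29 | about -0.28 | 17% |
| 0.75 | -0.80×0.0448/0.2245 = -0.16 | -0.15 | about -0.14 | 4% |
| 1 | 0 | 0 | 0 | 1% |

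**Step 3, sensitivity.** Here the total CV of per-kg LiMAx is fixed at 0.21 or 0.28, weight CV is varied from 15% to 20%, and the weight-BMI correlation is 0.85. Then rho is -0.44 to -0.80 (b=0), -0.22 to -0.39 (b=0.5), -0.11 to -0.20 (b=0.75) and 0 (b=1). The pattern is stable; the size at b=0 is not.

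**Step 4, other measures.** The artefact scales with the measure's correlation with weight. For a measure with an assumed correlation of 0.5 with weight, the formula value at b=0.5 is about -0.29×0.5/0.80 = -0.18.

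**Step 5, LiMAx against HFF.** This also needs an HFF-BMI correlation, which the article does not give. At an assumed 0.4, the induced rho is about -0.19 (b=0) to -0.06 (b=0.75). At n = 25, p<0.01 needs about 0.505 and is reached in at most about 5% of studies.

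**Step 6, candidate remedies.**
- Conditioning on weight returns rho to between about -0.03 and 0.00.
- Absolute LiMAx errs the other way: rho with BMI is about 0 at b=0 but about +0.48 at b=1.
- Power for a true effect: take capacity proportional to weight, a BMI elasticity of -1, noise log SD 0.20 and n = 32. The planned per-kg test finds it at p<0.01 in 90% of studies, the weight-partial in about 44%, and absolute LiMAx in about 2%.

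**The case against.** The strongest reply is that the sign and size rest on an exponent the article never gives. That stands: at b=1 there is no artefact, and at 0.75 the false-positive rate is about 4% against a nominal 1%. A reader might infer that any ratio must correlate negatively with its own denominator; it need not. The article does say that resecting a share of functional liver volume lowers LiMAx equivalently. That makes b<1 plausible where extra weight is fat, but this is inference.

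A reader might also infer that the adipose and muscle measures contain weight as BMI does. They do not; they are only correlated with it.

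A third tempting reading is that the artefact undermines the LiMAx-HFF relation and the choice between Hypotheses A and B. The article does not support that. It rests that question on repeated measurements over time, its main analysis is intrapatient change, and the leak in Step 5 is small. A stable difference in weight between patients cancels from relative within-patient change. Weight change during chemotherapy is a different matter.

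It can also be said that per-kg is the scale of the cited LiMAx data, that an inverse relation with BMI is true on that scale, and that an analysis plan not shown may adjust for weight. The first two are fair and are reasons to keep the planned correlation. The third does not remove the point, because the article itself names both the unadjusted method and the variables.

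**Conclusion.** The point holds for LiMAx against BMI, as a conditional risk to a named secondary outcome. Under the stated assumptions the built-in rho runs from about -0.5 if capacity is unrelated to weight to 0 if it is proportional. The chance of p<0.01 falls correspondingly from about 60% to the nominal 1%. It is weaker for body-composition measures in so far as they follow weight less closely than BMI does, and minor for LiMAx against HFF. The primary outcomes are not touched by this between-patient coupling. The conclusion rests on the assumed weight and height spread and on b<1, none of which the article reports. It does not show that a negative LiMAx-BMI correlation in this study would be false, only that it could not be interpreted on its own.

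**What to change.** Keep the planned per-kg Spearman correlations. For LiMAx against BMI and the body-composition measures, add two companion sensitivity results at each visit:

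1. the partial Spearman correlation given body weight at that visit;
2. the correlation with absolute LiMAx (per-kg value × weight).

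State in advance that a per-kg LiMAx-BMI correlation alone will not be read as evidence of impaired liver function. Do not require an association to hold on both scales: absolute LiMAx is biased in the opposite direction, and in Step 6 such a rule would discard nearly every true effect.

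The cost is a few lines of code; weight should already be at hand, because BMI is a planned measure. The real downside is power. With a weight-BMI correlation of 0.80, conditioning on weight leaves about 1 - 0.80² = 36% of the variance of log BMI, and this comes through height. A null partial correlation should therefore be reported as inconclusive, not as evidence of no association.

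### Both power figures are set at alpha 0.05 and match a two-group formula, while the plan declares significance at p<0.01 for within-patient change in one cohort

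*Protocol article*

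**What the plan says.** All of this stands in the protocol article under Statistical analysis and power calculation.

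- **HFF.** Baseline: "Our previous work reported a mean (±SD) HFF of 4 (±2")%. After chemotherapy: "increase to mean (SD)=6%±2.5"%. Evaluable patients: "25 patients will have complete data from at least 2 MR evaluations". Power: "The resultant power is 98% (alpha: 0.05; within-person correlation: 0.7").
- **LiMAx.** Inputs from a published study: "mean (±SD): 340±95 vs 391±82 µg/kg/hour". Evaluable patients: "we estimate at least 32 patients (10% attrition rate) will have complete data from two LiMAx tests". Power: "the resultant power is 84% (alpha: 0.05; within-person correlation: 0.7").
- **Significance rule.** "To account for multiple testing, a p value of <0.01 will be considered to indicate statistical significance".

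The section describes the main analysis as change within each patient in LiMAx and HFF. Under Primary outcome measures, these two changes are the primary outcomes. Under Study design, the study is non-randomised and observational, with no comparison group. The only other threshold is p<0.05, used to choose variables within clusters for the final regression model; it does not concern the primary changes.

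**The concern.** The sample size is justified at one threshold and the results are to be judged at another. A LiMAx change with p=0.03 would count as significant under the power statement and as not significant under the significance rule. If this is left open, the choice between them for a primary outcome could be made after the data are seen.

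The power figures are also the only stated justification for 35 patients. A reader takes 98% and 84% to be the chance of detecting the planned changes by the planned test. They are not, because the alpha differs and because the formula that yields them belongs to a different design.

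**Working it through.** **Inputs** (all from Statistical analysis and power calculation). HFF: difference 6 − 4 = 2 points, SDs 2 and 2.5, n = 25. LiMAx: difference 391 − 340 = 51, SDs 95 and 82, n = 32. Within-person correlation r = 0.7. The protocol does not state sidedness; two-sided is assumed throughout.

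**Step 1: reproduce the stated figures.** Take a change-score comparison between two independent groups, with n as the size of each group and a normal approximation:

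SE² = 2(1 − r)(SD₁² + SD₂²)/n; power ≈ Φ(difference/SE − z), with z = 1.960 at alpha 0.05.

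- HFF: SE² = 0.6 × (4 + 6.25)/25 = 0.246; SE = 0.496; 2/0.496 = 4.032; power **98.1%** (stated 98%).
- LiMAx: SE² = 0.6 × (9025 + 6724)/32 = 295.3; SE = 17.18; 51/17.18 = 2.968; power **84.3%** (stated 84%).

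Both match. Other formulas were tried with the stated inputs: paired (one- and two-sided), independent groups ignoring the correlation, covariance-adjusted, and half of n per group. None matches both figures.

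**Step 2: the test that fits the design.** For change within patients in one cohort, use a paired t-test and the noncentral t distribution:

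SD_diff² = SD₁² + SD₂² − 2·r·SD₁·SD₂; noncentrality = √n × difference/SD_diff.

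- HFF: SD_diff² = 10.25 − 1.4 × 5 = 3.25; SD_diff = 1.803; standardised change 1.109; noncentrality 5.547 on 24 df.
- LiMAx: SD_diff² = 15749 − 1.4 × 7790 = 4843; SD_diff = 69.59; standardised change 0.733; noncentrality 4.146 on 31 df.

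**Step 3: power at each threshold.**

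| Basis | HFF, n=25 | LiMAx, n=32 |
|---|---|---|
| Stated in protocol (alpha 0.05) | 98% | 84% |
| Two-group formula, r=0.7, alpha 0.05 | 98.1% | 84.3% |
| Two-group formula, r=0.7, alpha 0.01 | 92.7% | 65.2% |
| Paired test, r=0.7, alpha 0.05 | 99.96% | 98.0% |
| **Paired test, r=0.7, alpha 0.01** | **99.5%** | **91.1%** |
| Paired test, r=0.5, alpha 0.01 | 93.1% | 68.6% |

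For LiMAx, the two mismatches pull in opposite directions. The two-group formula understates power by about 14 points (84% against 98.0%), and the stricter threshold then takes away about 7 (98.0% to 91.1%).

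**The case against.** The strongest reply is that the stricter threshold does no harm on the protocol's own inputs. With r = 0.7, a paired test at 0.01 has more power for both outcomes than the protocol claims. The chance of missing the planned LiMAx change is about 9%, below the 16% implied by the stated 84%. This stands, and it limits the point to wrong figures and an unreconciled threshold.

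A second reply is that 0.01 may have been meant only for the per-timepoint tests and the correlation matrices. The sentence comes straight after these, just before the exploratory regression models, and gives multiple testing as its reason. That reading is plausible, but the text does not limit the rule in this way and sets no separate alpha for the primary outcomes. As written, the rule covers them.

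Nor can the point be set aside as detail for a separate analysis plan. Both thresholds are fixed in this article, and an analysis plan would have to depart from one of them.

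**Conclusion.** The point holds: 98% and 84% are not the power of the primary tests as written. The alpha is 0.05 where the significance rule says 0.01, and the figures match a two-group comparison that the study does not make. On the stated inputs, with a paired test at two-sided alpha 0.01, power is about 99.5% for HFF and 91.1% for LiMAx.

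A reader might infer that the study is underpowered for LiMAx, and the documents do not support that. One route is to carry the two-group formula to 0.01, which gives 65.2%, but that describes a comparison this cohort does not provide. Another is to force a paired test to return 84% by lowering the correlation to about 0.44, which leads to about 63% at 0.01 (type II error about 37%). The protocol states r = 0.7 for both outcomes, and Step 1 explains the 84% without any lower correlation.

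The conclusion rests on two-sided testing, the expected 25 and 32 complete pairs, and r = 0.7. The last matters most: at r = 0.5 and alpha 0.01, LiMAx power is 68.6%, while HFF stays at 93.1%.

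**What to change.** Correct alpha and formula together, since restating at 0.01 with the two-group formula would only carry the second mismatch forward.

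- If p<0.01 applies to the primary outcomes, restate power for a paired comparison at two-sided alpha 0.01: about 99.5% for HFF (n=25) and 91.1% for LiMAx (n=32) at r = 0.7. State the sidedness, and give the values at a lower correlation alongside (r = 0.5: 93.1% and 68.6%).
- If 0.01 was meant only for correlations and exploratory models, say so in one sentence and state the alpha for the two primary outcomes. If that is 0.05, paired power is 99.96% and 98.0%.

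Either way, settle it before the data are analysed. The cost is a sentence or two and two recalculated figures; on the stated inputs, no extra patients or procedures are needed.

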### Primary outcome measures

Change in liver function measured by the LiMAx test performed using the FLIP device, comparing baseline measurements with measurements during and after chemotherapy.Change in liver fat as a percentage (HFF) measured by advanced MRI (using both MRS and the modified Dixon method), comparing baseline measurements with measurements during and after chemotherapy.

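### Exploratory predictor models for HFF screen most candidates without the patient's baseline HFF, which costs power to find predictors of fat gain

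*Protocol article*

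**What the plan says.** All of this is in the Protocol article; no analysis plan is shown.

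- **Question.** Under Primary outcome measures, the HFF outcome is "Change in liver fat as a percentage (HFF) measured by advanced MRI", "comparing baseline measurements with measurements during and after chemotherapy". Under Statistical analysis and power calculation: "The main analysis will focus on intrapatient change in both liver function" and HFF, with ANOVA and mixed-effects methods to be explored. The Advanced MRI section contrasts this study with the group's earlier cross-sectional work on the ground that it follows change over time.
- **Predictor regression.** "Predictors of HFF at each timepoint will be explored using multivariable linear regression models". The outcome is a level, not a change.
- **Clusters.** "There will be at least five clusters: patient-related factors; routine blood measures; CT-derived anthropometrics; LiMAx readouts and MR readouts".
- **Selection.** "Separate models will be developed for each cluster and significant (p<0.05) variables selected for the final model".
- **Significance.** "To account for multiple testing, a p value of <0.01 will be considered to indicate statistical significance".
- **Planning values.** HFF of 4% (SD 2) before and 6% (SD 2.5) after chemotherapy, 25 patients with at least two MR evaluations, and "alpha: 0.05; within-person correlation: 0.7".

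Baseline HFF is not named as a covariate in any cluster model or in the final model. It is not excluded either.

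**The concern.** HFF is an MR readout, so a patient's baseline HFF belongs to the MR cluster. If each cluster has its own model, the patient-factor, blood, anthropometric and LiMAx screens are run on post-baseline HFF without it. Two things follow.

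1. A variable that predicts how much fat a patient gains is tested against residual variation that includes how fatty the liver already was. If it fails the p<0.05 screen it is not considered again.
2. A variable that only marks who had a fatty liver before treatment can pass the screen and enter the final model as a candidate predictor.

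The first matters more, because nothing later in the procedure undoes it. With about 25 informative patients there is little power to spare.

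**Working it through.** **The plan's own figure.** SD of the paired difference = √(2² + 2.5² − 2×0.7×2×2.5) = √3.25 = 1.803. Noncentrality = (2/1.803)×√25 = 5.55. A two-sided paired t-test at 0.05 has power 99.96%. The article states 98%, which is within two points and on the cautious side. The inputs are therefore used as given.

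**Variance shared with baseline.** 0.7² = 0.49. Adjusting for baseline HFF reduces the residual SD of follow-up HFF from 2.5 to 2.5×√(1 − 0.49) = 1.79.

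**Power at the screen.** Assume a predictor X unrelated to baseline and worth d HFF points per SD. Its correlation with follow-up HFF is d/2.5, and its partial correlation given baseline is (d/2.5)/√(1 − ρ²). For d = 1.0 and ρ = 0.7 these are 0.40 and 0.56. X is tested singly with n = 25, without baseline (23 df) and with it (22 df). Simulation with at least 40,000 samples per setting is good to about one percentage point.

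| d (assumed) | ρ | level | without baseline | with baseline |
|---|---|---|---|---|
| 0.75 | 0.7 | 0.05 | 32% | 55% |
| 1.0 | 0.7 | 0.05 | 53% | 84% |
| 1.25 | 0.7 | 0.05 | 75% | 98% |
| 1.0 | 0.7 | 0.01 | 28% | 63% |
| 1.0 | 0.5 | 0.05 | 53% | 65% |
| 1.0 | 0.3 | 0.05 | 53% | 55% |

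**Markers of pre-existing fat.** Let X have correlation g with baseline HFF (assumed), with ρ = 0.7.

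- If X relates to follow-up HFF only through measured baseline, its correlation with follow-up is 0.7g. For g = 0.3, 0.5 and 0.6 that is 0.21, 0.35 and 0.42. X passes the unadjusted screen 17%, 41% and 57% of the time, against about 5% adjusted.
- If X correlates equally (g) with baseline and follow-up HFF, its partial correlation is g(1 − 0.7)/√((1 − g²)(1 − 0.49)) = 0.13, 0.24 and 0.32. The adjusted screen then passes it 9%, 21% and 33% of the time. At g = 0.5 the unadjusted rate is about 75%.

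**The whole two-stage procedure.** This used 6,000 runs per setting, n = 25, one outside candidate, and baseline HFF tested alone in the MR cluster.

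- Baseline HFF reaches the final model in about 98% of runs (75% if ρ = 0.5).
- A candidate acting only through baseline then ends significant at p<0.05 in 2–4% of runs.
- A true predictor with partial correlation 0.5, unrelated to baseline, ends significant in 40% of runs, against 73% with baseline in the model throughout. Its screening rate alone is 43%, so nearly all of the loss occurs at the screen.

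**The case against.** **The omission is inferred.** A reader might conclude that the four non-MR models cannot contain baseline HFF. The text does not say so. It lists at least five groups of candidates, and grouping candidates does not bar a common covariate. The cluster paragraph also names no outcome; linking it to HFF relies on the regression sentence shortly before it. This stands, and limits the point to the procedure as laid out. The article does, however, state the outcome type, the grouping, the threshold and the selection rule, so the comment addresses a stated method and not a missing detail.

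**The target is HFF, not change.** A body-composition measure that tracks pre-existing fat is a genuine correlate of total HFF after chemotherapy, and total fat before resection has clinical interest. Change is analysed separately. This also stands: the 41% is a false-positive rate only if the result is read as predicting change. That reading is likely, since change is the study's declared question.

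**False predictors.** A reader might infer that the final model will be filled with them. The two-stage run does not support this: few stay significant once baseline HFF is present. They could persist if collinear MRS and mDixon readouts displaced baseline HFF from the MR cluster, but the article does not settle that.

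**Adjustment is one choice among several.** For non-randomised predictors, baseline adjustment and change scores answer different questions. Under the equal-correlation structure a change-score test holds 5% while the adjusted test does not. This stands. Adjustment still selects such variables far less often than no adjustment.

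**The power gains are favourable cases.** Predictors are tested singly and assumed independent of baseline, and 1.25 points per SD means a partial correlation of about 0.70. At ρ = 0.3 the gain almost disappears. This is accepted and shown in the table.

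**Conclusion.** The point holds in a limited form. Followed as laid out, the exploratory predictor analysis screens four of the five named clusters against post-baseline HFF without baseline HFF. The lasting harm is lost power for predictors of fat gain that are independent of baseline: 53% against 84% at the screen for an assumed 1.0 point per SD, or 40% against 73% through both stages for a partial correlation of 0.5. Over-selection of markers of pre-existing fat is real at the screen but mostly corrected later if baseline HFF enters the final model.

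The correlation, follow-up SD and n = 25 are the plan's. Using 25 assumes that those patients' scans include the baseline one. Predictor effects and predictor–baseline correlations are assumptions. The size of the loss depends strongly on the within-person correlation.

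A reader might take this as a flaw in the primary analysis. It is not: intrapatient change has its own analysis, and these regressions are described as exploratory. The change is worth making because it costs so little.

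**What to change.** Add to Statistical analysis and power calculation: for every timepoint after baseline, the patient's baseline HFF (same MR technique and same scale, logged if the outcome is logged) is included in each cluster model and in the final model, and is not subject to the p<0.05 selection. Describe the results as predictors of HFF given baseline.

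An unadjusted post-baseline regression may be kept as a descriptive analysis of total HFF, labelled as such. Models at the baseline timepoint need no adjustment.

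The cost is one degree of freedom per model and the exclusion of patients without a baseline scan, who cannot inform change in any case. No new data are needed.

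### Predictors of HFF are screened at p<0.05 by cluster and refitted in the same 25 to 35 patients, so the final model's p-values are conditional on selection and its R² is too high

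*Protocol article*

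**What the plan says.** All of this stands in the protocol article, under Statistical analysis and power calculation.

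- The target is HFF, modelled separately by visit: "Predictors of HFF at each timepoint will be explored using multivariable linear regression models".
- The reason for grouping the variables: "Because of the large number of variables and the anticipated high levels of correlations, we will use factor-cluster methods".
- The groups: "There will be at least five clusters: patient-related factors; routine blood measures; CT-derived anthropometrics; LiMAx readouts and MR readouts".
- The selection rule: "Separate models will be developed for each cluster and significant (p<0.05) variables selected for the final model".
- The general significance level, one paragraph earlier: "To account for multiple testing, a p value of <0.01 will be considered to indicate statistical significance".
- The patients available: "We have planned a recruitment of at least 35 patients", of whom "we conservatively estimate that 25 patients will have complete data from at least 2 MR evaluations". For the other measure, "we estimate at least 32 patients (10% attrition rate) will have complete data from two LiMAx tests".

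The section does not give the number of candidate variables. It mentions no separate validation sample, shrinkage, resampling or optimism correction for the final model.

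**The concern.** A variable that enters a model because its p-value was small will tend to show a small p-value again when it is refitted in the same patients. The second p-value no longer has its nominal meaning, and the R² of the final model counts chance fit as explained variance. Both effects are large when there are many candidates and few patients, which is the situation the section describes.

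The two thresholds also fit together poorly. The section adopts 0.01 because of multiple testing, but the step that searches through the most variables uses 0.05 without adjustment.

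At stake is how the predictor models are read. A final model with significance labels invites readers to treat its terms as established determinants of liver fat and its R² as predictive performance.

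**Working it through.** **Plan's own figure.** There is none for this procedure. The 98% and 84% powers in the section concern the before-after comparisons and do not bear on it.

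**Inputs from the document.** Screen at 0.05; significance at 0.01; at least five clusters; 25 patients with at least two MR evaluations; 35 recruited.

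**Assumptions.** The candidate count k is not given, so 10, 15 and 25 are used (two, three and five per cluster). No candidate is truly related to HFF. Correlation within a cluster is 0.5 unless stated, and clusters are independent.

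**Step 1: closed form.** For k independent null tests, the chance that at least one passes level a is 1 − (1 − a)^k.

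- At a = 0.05: 1 − 0.95^10 = 40%; 1 − 0.95^15 = 54%; 1 − 0.95^25 = 72%. The value first exceeds 50% at k = 14 (51%).
- At a = 0.01: 1 − 0.99^10 = 9.6%; 1 − 0.99^15 = 14%; 1 − 0.99^25 = 22%.

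**Step 2: simulation of the stated rule.** Fit one linear model per cluster, keep variables with p<0.05, and refit the kept variables together in the same patients. With 3,000 runs the standard error near 50% is √(0.25/3000) = 0.9 percentage points, so differences of a point or two mean nothing.

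| Candidates (n=25) | Any variable kept: formula | Any variable kept: simulated | Any at p<0.01: formula | Any at p<0.01 in final model: simulated |
|---|---|---|---|---|
| 10 | 40% | about 36% | 9.6% | about 10% |
| 15 | 54% | about 51% | 14% | about 14% |
| 25 | 72% | about 67% | 22% | 20–21% |

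Moving from n=25 to n=35 hardly changes the chance that something is kept (66% with 25 candidates).

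**Step 3: p-values of the variables that were kept.** If refitting left each p-value unchanged, a kept null variable would have p<0.05 every time and p<0.01 in 0.01/0.05 = 20% of cases. In the simulation it has final p<0.05 in about 50–65% of cases and p<0.01 in about 21%. Valid p-values would give 5% and 1%. With other cluster sizes and correlations from 0 to 0.8, the first figure ranges over 42–80% and the second over 19–24%.

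**Step 4: the p<0.01 rule, per candidate and overall.** With 25 candidates, 1.23 null variables enter on average, and a share of 0.205 of them reach p<0.01. Per candidate this is 1.23 × 0.205 / 25 = 1.0%. Applying p<0.01 directly in the cluster models, with no second stage, gives at least one false positive in about 20% of runs, much the same as the two-stage rule. The 10–21% in the table is therefore mostly multiplicity across candidates.

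**Step 5: R².** The truth is 0. When at least one variable is kept, mean apparent R² is about 0.24 (10 candidates) to 0.27 (25 candidates) at n=25, and about 0.20 at n=35 with 25 candidates. Counting runs with nothing kept as 0, the n=25 averages are 0.24 × 0.36 = 0.09 and 0.27 × 0.67 = 0.18.

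**The case against.** The strongest reply has four parts.

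- **The modelling is exploratory.** The section says predictors will be explored, and its main analysis is intrapatient change. This stands. A reader might infer that the primary results are compromised, but they do not pass through this selection step.
- **A false predictor is not shown to be the usual result.** A reader might infer that the final model will usually contain one. The document says only that the variables are many. With 10 null candidates the chance is about 36%, and with 15 it is about even. If variables were screened one at a time with within-cluster correlation 0.8, it would be 41–42% with 15 candidates and about 50% with 25. Some candidates may also be truly related to HFF. This stands, so the claim must be tied to a candidate count.
- **The p<0.01 rule still does something.** It is tempting to set about 21% against a nominal 1% and conclude that screening defeats the rule. The chance of any false positive among 25 candidates is not comparable with a level per test. Per candidate the rate stays near 1%. What remains is that the rule does not control error across candidates, and that a p-value in the final model cannot be read at face value for a variable already selected.
- **Factor-cluster methods are named, and the sample may exceed 25.** Grouping would help if each cluster were summarised without using HFF, but the text then selects individual variables on their p-values. The figure of 25 refers to patients with at least two MR evaluations. A model at one timepoint needs a single scan and could include up to those recruited. At 35 the R² inflation is smaller, and the selection problem is the same.

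A reader might also infer that chance decides which of several correlated variables survives. The simulations contain only null candidates and do not test that, so it is not claimed here.

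**Conclusion.** The concern holds in limited form. The protocol fixes a selection method that gives conditional p-values and an inflated R² in the final HFF models, whatever the number of candidates. The sizes above rest on all candidates being null, on within-cluster correlation of 0.5, and on one model per cluster.

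On those assumptions a final model holding a false predictor becomes more likely than not, per timepoint, only from about 15 candidates upward. Because the models are repeated at each timepoint, the chance over the whole study is higher.

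This is a poor stated choice for an exploratory analysis and should be changed. It gives no reason to doubt the planned before-after comparisons of LiMAx and HFF.

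**What to change.** Drop the p<0.05 screen and adopt one of two routes:

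1. Pre-specify two or three predictors in a single model of post-chemotherapy HFF.
2. Reduce each cluster to a score without using HFF (for example, its first principal component) and fit a penalised regression on the scores.

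If the screen is kept, bootstrap the whole process, including the cluster models and the selection. Report optimism-corrected R² and the frequency with which each variable is selected, and do not present the final-model p-values as confirmatory.

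Tightening the screen to 0.01 is not enough. With 25 null candidates false entry falls to about 20%, but at correlation 0.5 about 36% of the variables that do enter then show final p<0.01.

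In every case, state the candidate list and its length, and label the output hypothesis-generating. The cost is a change of analysis wording and some analysis time, with no new data or visits. The downside is that fewer predictors will be called significant.
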